## Protocol Deviations

All important deviations related to study inclusion or exclusion criteria, conduct of the

trial, patient managements or patient assessment will be described.

Protocol deviations will be categorized as:

Those who entered the study even though they did not satisfy the entry criteria.

Those who developed withdrawal criteria during the study but were not withdrawn.

Those who received the wrong treatment or incorrect dose.

Those who received excluded concomitant treatment.

## Ethical considerations

### Ethics, Data Security and Biobank

The study will be organized as a subproject in the BRAIN study, which is approved by the Regional Committee for Medical Research Ethics and the Norwegian Data Inspectorate. The bio bank is organized together with the Norwegian TOP (Thematic Organized Psychosis Research) study and has been approved by the Health Inspectorate. The bio bank is located at the National Institute of Health and the Database and protocol for the Person Data Security is approved by the Norwegian Data Inspectorate. There is a separate consent for this intervention study, which is also approved by the Regional Committee for Medical Research Ethics.

The patients included are severely ill, and in need of treatment considered to be effective in treatment resistant depression. ECT and the combination of antidepressant (including irreversible MAOI), atypical antipsychotics and a mood stabilizer are considered to be the treatment of choice in these patients. This means that both patient groups will receive adequate antidepressant treatment for their disorder, but will have a superior clinical management to patients not participating in a study. As stated in the exclusion criteria, some patients (e.g. acutely suicidal patients, post partum depression) should be offered ECT directly.

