#### Inclusion and exclusion criteria

The inclusion criteria were designed to ensure that the included patients are typical for patients referred to ECT in Norway in order to have results that are clinically significant, while the exclusion criteria are designed to ensure the patients' safety. Inclusion and exclusion criteria are shown in table 1 and 2.

**Table 1 T1:** Inclusion criteria

Diagnosis of DSM-IV-TR [52] of Bipolar I or Bipolar II disorder as verified by the semi-structured diagnostic interviews SCID [37] or MINI plus [36]. The diagnosis may be supported by information from significant others, and from hospital records. Angst's hypomania checklist [53] is used to increase the detection of hypomanic symptoms. SCID or MINI plus will be used to diagnose the patient.
ECT is indicated.
Severity: meet DSM-IV-TR criteria of depressive episode, MADRS [40] of 25 or above
Treatment resistance: None response to two trials (during lifetime) with mood stabilizers with proven efficacy in bipolar depression (lithium, lamotrigine, quetiapine, olanzapine) and/or antidepressants.
A trial is defined as at least 6 weeks in adequate or tolerated dose as reported by the patient, or patients that have been unable to comply with 6 weeks trials of mood stabilizer or an antidepressant.
None response: Less than 50% reduction in MADRS values or still meet DSM -IV-TR criteria of depressive episode
Inpatients the first week after start of treatment condition
The patients are to be treated by the psychiatrist at the hospital for the whole duration of the study (6 weeks)
Age ≥ 18
Patient competent to give informed consent according to the judgement of the clinician
Written informed consent
Patient sufficiently fluent in Norwegian language to ensure valid responses to psychometric testing (for patients enrolled to neuropsychological assessment: Norwegian as primary language or 12 years attendance of a Norwegian school)

**Table 2 T2:** Exclusion Criteria

Earlier ECT none response
ECT within the last six months
Rapid cycling BD (e.g.4 or more episodes per year)
Use of medication or substances (such as pethidine, alcohol, drugs) incompatible with treatment (medication or ECT). Such medication must be stopped a least 5 half-lives before start of treatment.

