Current use of all other psychotropic medication during the study period with the exception of the following: The use of alimemazine (max dose 30 mg daily), chlorpromazine (max dose 25 mg × 2 daily) and chlorprothixene (max dose 20 mg × 2) is allowed. The use of mianserine (max dose 10 mg daily) is allowed. Medication related to the ECT procedure is allowed.
For Medication in control group refer to Medication in control group - Treatment As Usual
Inability to comply with study protocol
Unstable serious medical conditions, including clinically relevant laboratory abnormalities
Conditions that affect neuropsychological assessment such as Parkinson's Disease, Multiple sclerosis, stroke, alcohol and substance abuse or dependence (according to SCID or DSM-IV-TR)
Fertile women without adequate contraception (Adequate contraception includes: abstinence, oral contraceptives, intrauterine devices, barrier method)
Young Mania Rating Scale (YMRS) [43] of 20 or more
Patient at high suicidal risk according to clinicians' judgement

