### Inclusion, randomization and masking of study groups

All patients suffering from a major depressive episode admitted to one of the nine study centres are evaluated for inclusion. During the screening the local participating psychiatrist will determine whether the patient fulfils the inclusion criteria and none of the exclusion criteria. Patients will be randomly assigned to the two groups. The randomization is stratified separately in each study centre. The patient and treating psychiatrist are unmasked about treatment modality. The assessments of depressive symptoms before and after ECT will be audio-taped. The audio-tapes will be co-rated by trained study personnel who are not involved in the treatment of the study patients. The analyses will be preformed on audio taped scores. There might be some patients who do not accept audio taping, in these cases investigator-rating will be used. Neuropsychological assessment is performed by trained test assistants who are blinded about treatment modality.

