### Description of treatment

#### Method of assigning patients to treatment groups/Randomization

Patients' eligibility will be established before randomization to one of the treatment options. Relevant patients with BD are addressed in order to establish whether they are willing to be screened for the study. The patients must be assigned a patient number and sign the consent form after receiving oral and written information about the study prior to undergoing any study procedures. Patients will be randomized strictly sequentially, as patients are eligible for randomization. If a patient discontinues from the study, the patient number will not be reused, and the patient will not be allowed to re-enter the study.

We perform a stratified randomization separately for each centre using the default random number generator of SPSS 15 with a random seed. The randomization lists are kept concealed from the investigators.

After randomization patients will enter a wash out phase if necessary. The recommended time for patients to be without concomitant medication in contradiction to the study protocol is 5 t 1/2 for patients randomized to ECT and a varying time for patients randomized to treatment as usual.

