### Methodological weaknesses

The use and policy regarding ECT differs between countries and hospitals. Thus there are no published guidelines defining objective clinical criteria for indications of treatment with ECT in bipolar depressions. In the present protocol "indication for ECT" is one of the inclusion criteria. This means that treatment with ECT would have been probable according to hospital practice regardless of the present study.

The assessments are performed by specially trained research staff which is not blinded for grouping of the patients. Most of the patients are acutely admitted to psychiatric acute wards due to the extensive symptom pressure.

The multicentre site design has potential problems regarding assessments and inter-rater reliability. However, multicentre design is a necessity in order to include sufficient number of patients in a reasonable time span. All raters and participants in the study have taken part in mutual training-sessions in the different assessments and rating scales. All participants have taken part in interrater-scorings. The scorings for the different study centres and the different participants are satisfactory.

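### The ethics section cites an exclusion for post partum depression that Table 2 does not contain

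*Protocol article*

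**What the plan says.** The section Ethics, Data Security and Biobank argues that randomisation is acceptable because both arms receive adequate antidepressant treatment. It then describes patients who should not be randomised: "As stated in the exclusion criteria, some patients (e.g. acutely suicidal patients, post partum depression) should be offered ECT directly".

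The section Inclusion and exclusion criteria says where the criteria are: "Inclusion and exclusion criteria are shown in table 1 and 2". It also gives their purpose, "while the exclusion criteria are designed to ensure" patient safety.

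Two rows of Table 2 come closest to the groups named in the ethics section. One begins "Patient at high suicidal risk according to" and leaves the assessment to the clinician. The other begins "Fertile women without adequate contraception".

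On how the criteria are applied, the section Inclusion, randomization and masking of study groups says that at screening "the local participating psychiatrist will determine whether the patient fulfils the inclusion criteria and none of the exclusion criteria". The section on the method of assigning patients adds that "eligibility will be established before randomization to one of the treatment options".

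**The concern.** The ethics section does not merely express a clinical preference. It says that the exclusion criteria already contain the rule, and it relies on that rule in justifying the trial. If the criteria do not contain it, part of the ethical argument rests on a safeguard that the printed screening step does not apply.

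What is at stake is patient protection rather than inference. A woman with post partum bipolar depression who passes screening could be allocated to the drug algorithm. Under Study design, the other treatment is considered only after the six-week trial and outside the study, unless she leaves or is withdrawn sooner. With no written row, whether she is kept out depends on whoever screens at each of the nine centres. Enrolling her would also not count as an entry-criteria violation under Protocol Deviations, because no printed criterion would have been breached.

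**Working it through.** No arithmetic is needed for the contradiction itself, and the plan gives no figure to reproduce. The check compares the ethics section with the printed criteria.

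**Step 1: count the rows of Table 2.** Leaving out the line that only refers the reader to the control-group medication section, the exclusions are:

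1. earlier non-response to ECT
2. ECT in the previous six months
3. rapid cycling
4. incompatible medication or substances
5. other psychotropic medication, with listed exceptions
6. inability to comply
7. unstable serious medical conditions
8. conditions affecting neuropsychological assessment
9. fertile women without adequate contraception
10. YMRS of 20 or more
11. high suicidal risk

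**Step 2: match them to the two groups named in the ethics section.**

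| Group named | Rows in Table 2 |
|---|---|
| Acutely suicidal | 1 of 11 (row 11) |
| Post partum depression | 0 of 11 |

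One of the two named groups is covered.

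**Step 3: look for indirect cover.**

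- Row 9 concerns contraception, not recent delivery.
- Row 7 concerns medical instability and neither names nor implies post partum depression.
- Row 11 would catch post partum patients who are also at high suicidal risk, but not the others.
- Table 1, Withdrawal criteria and Procedures in case of pregnancy do not mention post partum status.

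**Step 4: test whether the inclusion criterion requiring an ECT indication diverts her.** It does not. Methodological weaknesses explains that criterion to mean that "treatment with ECT would have been probable according to hospital practice regardless of the present study". A patient who ought to have ECT satisfies it, so it helps her qualify.

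**Step 5: follow the process.** A patient who meets Table 1 and no row of Table 2 passes screening, and screening precedes randomisation. As printed, nothing in that sequence stops a post partum patient on account of her post partum status.

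**Step 6: size.** The target is 132 patients, so one patient is 100 × 1/132 = 0.76% of it. This is a scale for recruitment, not an estimate of risk. The article does not say how many post partum patients to expect. Entry also needs bipolar disorder, MADRS of 25 or above, two failed treatment trials, an ECT indication and inpatient status, so the number is likely to be very small and may be zero.

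**The case against.** The strongest reply is that this is a loose sentence in an ethics section, not a lost safety rule. The groups are introduced as examples, and Table 2 sends no excluded patient to ECT, not even suicidal ones; that direction appears only in the ethics section. This is a fair reading, and the article does not settle which text is wrong. But calling a group an example does not make it optional when the sentence says the criteria state it.

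Second, nobody need be screening from the journal table. The full protocol, the screening form and the synopsis in Additional file 2 are not shown, and any of them may list the exclusion. This stands as a limit: a gap in actual screening is not shown, only one in the printed criteria. It does not remove the contradiction, because the article makes a statement about its criteria that the criteria it prints do not bear out.

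Third, there are safeguards. Study design lets the patient or treating clinician end participation at any time after consent, which includes the period before randomisation. Withdrawal criteria goes further: once the clinician judges that other treatment would serve the patient better, withdrawal follows and is not optional. This protection is real. It still starts from an individual judgement and does not supply the exclusion the ethics section describes.

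Fourth, the suicidal-risk row also rests on clinical judgement. That is true, but the row prompts the screener to make that judgement. Nothing in Table 2 prompts the question of post partum onset.

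**Conclusion.** The concern holds, and it is minor. The ethics section attributes to the exclusion criteria a group that the printed criteria omit: one of two named groups is covered and one is not. Applied as written, Table 2 would not keep a post partum patient out of randomisation if she met the other criteria.

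The consequence is confined to eligibility and to the ethical justification. It probably concerns very few patients, possibly none. Sample size, power and the planned analyses do not change.

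The conclusion assumes that Table 2 as printed is the full list, as the article says. If the full protocol has the row, the fault lies only in the article's table. If the exclusion was never intended, it lies in the ethics section.

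**What to change.** Settle the intent first, then change one text.

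- **If the exclusion is intended:** add a row to Table 2 and a line to the screening form excluding a current depressive episode with post partum onset, with a note that such patients are to be offered ECT directly. The sponsor must set the time window, since the article gives none. The cost is one row, one form line and perhaps a few otherwise eligible patients (0.76% of 132 each), who would be replaced in recruitment.
- **If it is not intended:** delete the three-word example from the sentence in Ethics, Data Security and Biobank. This costs nothing, but it only tidies the text and adds no protection.
- **If the full protocol already lists it:** correct the article's Table 2 to match.

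Given the safety purpose stated for the exclusion criteria, adding the row is preferable unless the sponsor confirms that these patients were meant to be eligible.

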### Ethical Conduct of the Study

The study is conducted in accordance with the ethical principles that have their origins in the Declaration of Helsinki.

### Patient Information and Consent

Informed consent will be obtained after the investigator has verbally explained the purpose and procedures involved in the study, answered questions, and otherwise provided information that permits the patient to make a prospective, informed decision. Informed consent will be signed and dated before any study data collection procedures begin.

A synopsis of the study protocol is given as additional file 2.

## Discussion

This study protocol presents a randomized controlled trial for a population of in-patients with serious, therapy resistant bipolar depressions. We believe that this study is important and needed, and that the main results may influence daily clinical practise. Both bipolar depression and the treatments for bipolar depression are associated with cognitive impairments. This study may give important information of short-and long-time contributions and effects of these different factors.

### Methodological strengths

The present study is strengthened by the prospective design. All participating study centres include patients from their defined catchment areas. All Norwegian acute psychiatric services are public and available to everyone. All the patients in the catchment areas are admitted to the local study centre. Acute admissions to other psychiatric hospitals occur only when inhabitants temporarily reside outside of the catchment area at the time of admittance.

We use robust and validated diagnostic and psychometric instruments. Both in the study and control groups the procedures and registrations for each patient are comprehensive. The collection of background data with the NEQ makes it possible to compare the present bipolar population with bipolar populations in other clinical trials.

### Methodological weaknesses

The use and policy regarding ECT differs between countries and hospitals. Thus there are no published guidelines defining objective clinical criteria for indications of treatment with ECT in bipolar depressions. In the present protocol "indication for ECT" is one of the inclusion criteria. This means that treatment with ECT would have been probable according to hospital practice regardless of the present study.

The assessments are performed by specially trained research staff which is not blinded for grouping of the patients. Most of the patients are acutely admitted to psychiatric acute wards due to the extensive symptom pressure.

The multicentre site design has potential problems regarding assessments and inter-rater reliability. However, multicentre design is a necessity in order to include sufficient number of patients in a reasonable time span. All raters and participants in the study have taken part in mutual training-sessions in the different assessments and rating scales. All participants have taken part in interrater-scorings. The scorings for the different study centres and the different participants are satisfactory.
